Validated measures will be used to assess these proposed mediators of adherence. Skills will be measured with five constructs: perceived competence, glaucoma knowledge, self-efficacy, goal setting, and confidence asking the physician questions. Perceived competence [59] (four items, Cronbach *α* = 0.80) assesses participants’ perceptions of how able they are to manage their glaucoma on a seven-point Likert scale. Perceived competence will be measured at the baseline, 6-, 12-, and 24-month study visits. Glaucoma Knowledge will be assessed with a 10-item true/false test generated by the National Eye Institute (NEI) [60]. Glaucoma knowledge will be measured at the 3- and 8-month study visits, before and after the eyeGuide intervention, respectively, and at the 24-month study visit. Glaucoma medication and eye drop instillation self-efficacy [61] (medication self-efficacy, 10 items, eye drop instillation self-efficacy, 6 items, *α* = 0.91 for all 16 items) assess participants’ self-confidence in using their eye drop medications as prescribed and instilling them into their eyes correctly using a three-point Likert scale. Glaucoma medication and eye drop instillation self-efficacy will be measured at the baseline, 6-, 12-, and 24-month study visits. Goal setting (three items, *α* = 0.80) measures whether or not health care providers asked participants to set goals to improve how they take care of their chronic disease on a five-point Likert scale. The Goal Setting Scale is a sub-scale of the Patient Assessment of Chronic Illness [62] measure. We could not use the full sub-scale as the final two questions ask if the person has been asked to attend a class to help cope with their chronic condition or asked to fill out a survey about their chronic condition, neither of which are standard aspects of current glaucoma care. Goal setting will be measured at the baseline study visit, and the 12- and 24-month study visits. Confidence asking the physician questions will be measured with three items from the adapted Perceived Efficacy in Patient-Physician Interactions Scale [63] (PEPPI, five items, α = 0.83) using a five-point Likert scale. Confidence asking the physician questions will be assessed at the baseline visit and the 12-month study visit.

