Energy for change will be measured with two constructs using two different scales, the Health Care Climate Questionnaire [65] (HCCQ; 12 items, *α* = 0.96) and the Treatment Self-Regulation Questionnaire [64] (TSRQ; 19 items, *α* = 0.81). The HCCQ measures perceived autonomy support from health care providers. The TSRQ measures whether a participant feels motivated to accomplish a health-related goal because of their own internal desires, such as “I personally believe that controlling my glaucoma will improve my health” or whether they take care of their health problem for reasons external to themselves, like “I want my doctor to think I’m a good patient.” Both of these scales have been validated in patients with diabetes and have been adapted to glaucoma, a similar chronic disease that requires consistent self-management for optimal disease control, for this study. Both scales use seven-point Likert scales. The HCCQ and TSRQ will both be given at the baseline, 6-, 12-, and 24-month study visits.

Satisfaction will be measured in two ways. Satisfaction with information about glaucoma will be measured using the Satisfaction with Information Scale [66] (four items). These questions were developed to assess how patients with hyperlipidemia felt about the type of information they received about their disease. The scale uses a seven point Likert scale to assess satisfaction with the amount of information received, the clarity of the information, how helpful the information was, and how well people now understood how to take their medications. The Satisfaction with Information scale will be given at the baseline study visit, and the 12-month study visit, at the conclusion of the eyeGuide intervention. Satisfaction with the eyeGuide intervention will also be measured at the 12-month study visit using the Client Satisfaction Questionnaire [67, 68] (three-item subscale, *α* = 0.91).

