^a^Time Point 1 = baseline (0 months), 2 = intervention 1 (alarms, 3 months), 3 = intervention 2 (eyeGuide, 6 months), 4 = eyeGuide follow-up visit (8 months), 5 = intervention end (12 months), 6 = end of adherence monitoring (24 months, end of study)

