### Statistical design

#### Data analysis

The primary outcome, adherence, captured by the electronic monitors, will be a continuous measure from 0 to 100 representing the percent of glaucoma medication doses taken on time over a specific time period. Baseline adherence for the 3-month interval before any intervention will be investigated for the Hawthorne effect. Because simply monitoring a patient can cause them to temporarily change their behavior, even in the absence of actual intervention [81], we will plot adherence over time for each patient during the first 3 months of monitoring. Previous electronic medication monitoring for glaucoma medications demonstrated that the Hawthorne effect wore off after approximately 40 days of monitoring, which is why we chose to monitor participants for 90 days [82]. We will investigate plots for patterns of better adherence during the initial weeks of monitoring and worse adherence during the later weeks of baseline monitoring. Additionally, we will compare adherence in earlier vs. later weeks using paired *t* tests. If a significant Hawthorne effect is found, we will use the third month of monitoring data as a baseline adherence score. Although using the worst month of adherence as a baseline score could expose us to regression to the mean, we would expect outliers in adherence to be random throughout the 3-month period and not necessarily bias the results in only the last month of monitoring. Adherence at baseline and after the intervention will be compared with paired *t* tests for all pair-wise comparisons. Adherence 1 year after the end of all interventions will be evaluated for stability. This will be investigated with plots, and analyzed with paired tests and linear mixed regression models (LMM).

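### For four psychosocial scales the only before-and-after-reminders comparison runs from month 0 to month 6, and half of that interval is run-in without reminders

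*Protocol article*

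**What the plan says.** Under Secondary outcomes, the protocol article defines the psychosocial outcomes as change in perceived glaucoma skills and in energy for change following each intervention. Data analysis repeats this commitment, with paired t tests for the continuous measures.

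The schedule is given scale by scale:
- Energy for change: "The HCCQ and TSRQ will both be given at the baseline, 6-, 12-, and 24-month study visits".
- Perceived competence: "Perceived competence will be measured at the baseline, 6-, 12-, and 24-month study visits".
- Self-efficacy: "Glaucoma medication and eye drop instillation self-efficacy will be measured at the baseline, 6-, 12-, and 24-month study visits".

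The footnote to Table 2 fixes the calendar: "Time Point 1 = baseline (0 months), 2 = intervention 1 (alarms, 3 months", with eyeGuide starting at 6 months. Baseline is therefore the consent visit. The opening of Methods/design describes the first three months as monitoring ahead of any intervention, partly to deal with regression to the mean and the Hawthorne effect. Data analysis gives the reason for adherence: "Because simply monitoring a patient can cause them to temporarily change their behavior, even in the absence of actual intervention".

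**The concern.** The run-in lets the design separate the effect of being observed from the effect of the first component. Adherence gets that benefit because its baseline is taken from the run-in. The four scales do not, because their before value is collected at consent, ahead of the run-in.

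At stake is what a change in these scales between month 0 and month 6 can be credited to. Participants enrol, complete a 60-minute survey, live with a monitor for three months and learn that they qualify, all before the first reminder. If any of this shifts perceived competence, self-efficacy, perceived autonomy support or motivation in a lasting way, the shift will be reported as change following reminders. The pilot is meant to show whether the intervention's impact is plausible before a randomized trial, so the component to which a change is attributed matters.

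**Working it through.** **Schedule against intervention periods** (Timeline; Component 1 and Component 2; Secondary outcomes; Table 2 footnote)

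| Period | Content | Four scales at start | Four scales at end |
|---|---|---|---|
| Month 0 to 3 | monitoring only | yes (month 0) | no |
| Month 3 to 6 | reminders | no | yes (month 6) |
| Month 6 to 12 | eyeGuide | yes (month 6) | yes (month 12) |

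The only value before reminders is month 0, and the only value after reminders alone is month 6. The interval is 6 months, of which 3 are run-in: 3/6 = 50%.

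**What the paired test estimates.** Let Y0, Y3 and Y6 be the scale at months 0, 3 and 6. Then

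mean(Y6 − Y0) = mean(Y3 − Y0) + mean(Y6 − Y3).

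The first term is run-in drift net of reminders, and the second is change during reminders. Y3 is never observed, so only the sum can be estimated. The mediator-on-time model in Data analysis fits one slope over all visits and cannot split the sum. A model with separate periods could not do so either, since there is no observation between months 0 and 6.

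**Which scales are affected.** Four: HCCQ, TSRQ, perceived competence and self-efficacy. The other skills measures differ:
- Goal setting has no month-6 value: "Goal setting will be measured at the baseline study visit, and the 12- and 24-month study visits".
- Question-asking confidence has none either: "Confidence asking the physician questions will be assessed at the baseline visit and the 12-month study visit".
- Knowledge starts after the run-in, but its next value falls after eyeGuide has begun: "Glaucoma knowledge will be measured at the 3- and 8-month study visits".

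None of these three gives a reminders-only change. The month 0 to 12 change in the first two does span the run-in.

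**Illustration of size.** The protocol states no drift for these scales, so the drift is an assumption.
- Inputs: n = 46 pairs (the Sample size section's figure for adherence, borrowed here), two-sided 5%, zero reminder effect, and persistent drift d in units of the SD of the paired change.
- Method: the paired t statistic is noncentral t with n − 1 = 45 degrees of freedom and noncentrality d × √46, where √46 = 6.782. The rejection rate is the probability of falling outside the two-sided 5% critical values.

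| d | Noncentrality | Declared significant |
|---|---|---|
| 0.1 | 0.678 | 10.2% |
| 0.2 | 1.356 | 26.4% |
| 0.3 | 2.035 | 51.2% |
| 0.4 | 2.713 | 75.6% |

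**Item count for a month-3 administration.** Perceived competence 4 + self-efficacy 16 (10 + 6) + HCCQ 12 + TSRQ 19 = 51.

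**The case against.** The strongest reply is that the effect of monitoring may not last. Data analysis calls it temporary and reports that, in earlier glaucoma monitoring, it faded after about 40 days. Month 6 is about 180 days (twice the 90-day run-in) after monitoring starts. If the scales behaved as adherence did, most of the shift would be gone by then. This stands to the extent that only a persistent change biases the contrast, so a reader should not infer that everything that happens in the run-in carries through to month 6. The 40-day figure concerns adherence, however, and nothing in the document shows how these scales behave.

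A reader might also infer that run-in change contaminates a reminder-specific step of the mediation analysis. The protocol has no such step: it tests a single slope over time. The model merely fails to separate the periods.

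The run-in also sets eligibility and limits regression to the mean, because participants are selected on monitored adherence. The four scales are not selection variables, so that part of the rationale does not transfer directly.

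Finally, the Discussion already names the missing control arm as the largest limitation and notes that monitored participants may change their behavior. That is a fair general caveat, but the Hawthorne check it points to covers adherence only. The run-in is the nearest thing this design has to a control period, and these scales do not use it.

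**Conclusion.** The point holds for four secondary scales and one contrast. Perceived competence, self-efficacy, HCCQ and TSRQ have no value at the start of reminders, so the promised change following reminders mixes three months of monitoring alone with three months of reminders. The gap is in data collection, so an analysis plan cannot repair it afterwards.

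The size of any bias is unknown. The 10% to 76% range shows how an assumed persistent drift of 0.1 to 0.4 SD would translate into false findings; it is not the plan's error rate. It would be wrong to extend the point to every psychosocial measure, since the others follow different schedules. The month 6 to 12 eyeGuide contrast, monitored adherence and the sample size are not affected.

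**What to change.** Give the four scales to continuing participants at the month-3 visit, after they are told they are eligible and before reminders are switched on. Define month 3 to 6 as the reminder contrast and month 6 to 12 as the eyeGuide contrast. If the month-0 administration is kept, report month 0 to 3 as the monitoring-only change.

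The order within the visit matters. If the scales came before notification, any reaction to it would fall inside the reminder contrast. Even in the right order, a slow reaction to notification could still do so.

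The cost is at most 51 items at a visit that already carries the self-reported adherence questionnaires, the knowledge test, the PHQ-9 and a literacy measure. Adding the scales makes that visit longer. Moving them from month 0 adds no items overall but gives up the only value from before monitoring. Either way the month 3 to 6 contrast remains uncontrolled: continued monitoring and drift over time still fall inside it, and the report should say so.

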#### Study specific adverse event reporting

Any physical, social, economic, or psychological harm attributable to participation in this research study, if serious, will be reported to the IRB within 7 days and any non-serious adverse events will be reported with scheduled continuing review. Examples of possible adverse events include an injury occurring during a study visit, depression identified during a study visit, breach of confidentiality, or auto accident on the way to or from a study visit. Any unrelated deaths while in the study will be reported to the IRB with scheduled continuing review.

Any clinical depression identified during the study will be handled according to our depression screening protocol (Additional file 4). Participants who have issues with medication adherence may have problems because of underlying psychological distress. Therefore, we will use the patient health questionnaire (PHQ-9), a validated measure used clinically to assess for depression [77], during the 3-, 10-, and 12-month study visits so that all participants are screened for depression annually and if a participant is identified as having depressive symptoms they will be referred to appropriate care (see protocol, Additional file 4).

Any increases in IOP will be managed by the study principal investigator ([name]) and study team but are not considered reportable events to the IRB. When the participant’s IOP is checked, if it is above the goal pressure that has been set for them by their physician, the study team will contact their ophthalmologist through the electronic medical record and via email to let them know and determine an appropriate follow-up with their ophthalmologist. If the participant’s IOP is > 21 mmHg, the PI will be paged and the participant will be seen immediately in the glaucoma clinic by a physician for further management if medically indicated.

#### Data and safety monitoring plan

As the study has been deemed to have minimal risk by the Institutional Review Board (University of Michigan, Ann Arbor, MI), the Institutional Review Board has recommended that members of the study team will review study recruitment, adverse events, and compliance with the protocol every 6 months.

### Statistical design

#### Data analysis

The primary outcome, adherence, captured by the electronic monitors, will be a continuous measure from 0 to 100 representing the percent of glaucoma medication doses taken on time over a specific time period. Baseline adherence for the 3-month interval before any intervention will be investigated for the Hawthorne effect. Because simply monitoring a patient can cause them to temporarily change their behavior, even in the absence of actual intervention [81], we will plot adherence over time for each patient during the first 3 months of monitoring. Previous electronic medication monitoring for glaucoma medications demonstrated that the Hawthorne effect wore off after approximately 40 days of monitoring, which is why we chose to monitor participants for 90 days [82]. We will investigate plots for patterns of better adherence during the initial weeks of monitoring and worse adherence during the later weeks of baseline monitoring. Additionally, we will compare adherence in earlier vs. later weeks using paired *t* tests. If a significant Hawthorne effect is found, we will use the third month of monitoring data as a baseline adherence score. Although using the worst month of adherence as a baseline score could expose us to regression to the mean, we would expect outliers in adherence to be random throughout the 3-month period and not necessarily bias the results in only the last month of monitoring. Adherence at baseline and after the intervention will be compared with paired *t* tests for all pair-wise comparisons. Adherence 1 year after the end of all interventions will be evaluated for stability. This will be investigated with plots, and analyzed with paired tests and linear mixed regression models (LMM).

LMMs will be used to investigate predictors of adherence. Variables investigated will include participant characteristics and demographics, clinical measures of disease severity, and counseling and health literacy measures. Repeated measures logistic regression with generalized estimating equations (GEE) will also be used to investigate predictors of adherence >/=80%. The repeated measures analyses (LMM and GEE) will use adherence data gathered over all time points and account for the correlation within an individual over time. Moderators of glaucoma medication adherence will be investigated in the LMMs by interactions with time, to test the hypothesis that moderators will have different slopes of medication adherence over time [83]. Mediators of glaucoma medication adherence will be investigated with a series of LMMs [83]. First, the effect of the intervention on glaucoma medication adherence will be tested. Because all participants receive the intervention, this will be a test of slope of medication adherence over time (*Y*_medication adherence_ ~ *X*_time_). Next, the effect of the intervention on glaucoma medication adherence after adjustment for a mediator will be tested (*Y*_medication adherence_ ~ *X*_time_ + *X*_mediator)_. Lastly, the effect of the intervention on a mediator will be tested (*Y*_mediator_ ~ *X*_time_). After standardizing the effects from these three models, the direct, indirect, and total effects of the intervention will be estimated and Sobel’s test will be used to test the significance of the indirect effect.

We will adjust for weekly and seasonal trends when assessing other factors influencing adherence. We will use time series analysis using the 2 years of daily adherence data for each patient. Using Unobserved Component Models (UCMs), weekly and seasonal (yearly) cycles will be identified and tested in the context of a comprehensive regression model that adjusts for covariates such as participant characteristics and study intervention period. After adjustment, we will test for trends, e.g., a gradual improvement in adherence over time or a drop in adherence post-intervention [84, 85]. The SAS procedures TIMESERIES and UCM will be used for these analyses. The UCM procedure handles missing values in the dependent series and provides model diagnostics.

Secondary outcomes include comparing adherence measured by pharmacy refill data, self-report, and successful eye-drop instillation to electronic monitoring using Pearson’s correlations. Changes in glaucoma skills and energy for change will be assessed after each intervention component and at 1 and 2 years post-intervention and compared with paired *t* tests and McNemar’s tests for continuous and categorical measures. All analyses will be conducted with SAS software, version 9.4 (SAS Institute, Cary, NC, USA).

The semi-structured interviews will be recorded and transcribed verbatim. Two investigators will read the transcripts and identify major themes. The data will be interpreted qualitatively using grounded theory [86]. A code book will be generated defining codes for each theme. Two investigators will then code the transcripts. Any areas of disagreement will be discussed until consensus is reached or adjudicated by a third researcher [87]. The coded content will be tallied to weight the frequency of the themes. The transcripts will also be analyzed by participant group, those who did and those who did not improve from the intervention. Themes from these two groups will be compared in a joint display to try to identify reasons why the program was not successful among some participants to identify areas for programmatic improvement.

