### Outcomes

#### Primary outcome

The primary outcome is change in medication adherence (continuous variable for percentage of medication doses taken on time) measured by electronic medication monitors after each intervention. We will also measure adherence by three additional techniques in order to reflect different aspects of adherence behavior [51] and compare the techniques to one another: (a) video-recorded drop instillation, (b) self-reported adherence [52–55], and (c) pharmacy refill data. To assess how well patients can properly instill their eye drops, we will video-record patients instilling their eye drops during their third and fifth study visits, before and at the end of the eyeGuide intervention, respectively. Two masked assessors will review the videos and assess each participant for the following three techniques: (1) does the participant dispense a single drop, (2) does the drop get into the eye, and (3) does the participant touch the dropper tip to the ocular adnexa or extraocular structures. Self-reported adherence will be assessed with the Morisky questionnaire [56] (eight items, Cronbach *α* = 0.83), the Adherence to Refills and Medications Scale [57] (ARMS, 12 items, *α* = 0.81), and three additional questions about adherence from the glaucoma literature [55, 51]. These adherence questionnaires will be given at the baseline, 3-, 6-, 12-, and 24-month study visits.

Pharmacy refill data will be obtained by calling each participant’s pharmacy every 3 months to identify whether each prescribed medication has been filled. The medication possession ratio (MPR) is the proportion of days during a fixed time period where the patient had an adequate supply of medication to use at the prescribed frequency. MPR will be calculated at the patient level after combining refill data from all medications during a defined time period, as follows:$$ \frac{\mathrm{MPR}=\kern0.5em \#\mathrm{days}\ \mathrm{correct}\ \mathrm{amount}\ \mathrm{of}\ \mathrm{medication}\ 1+\dots +\#\mathrm{days}\ \mathrm{correct}\ \mathrm{amount}\ \mathrm{of}\ \mathrm{medication}\ 4}{\#\mathrm{elapsed}\ \mathrm{days}\ \mathrm{medication}\ 1+\dots +\#\mathrm{elapsed}\ \mathrm{days}\ \mathrm{medication}\ 4} $$

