#### Sample size

We estimate that 46 participants will provide 80% power to detect at least a relative improvement of 15% in adherence (from an average pre- to post-intervention adherence rate of 0.7 to 0.8, and common standard deviation of 0.20) with a type-1 error rate of 5% and assuming a mild correlation of 0.3 between pre- and post-intervention adherences. We wanted adequate power to identify even a small effect size to evaluate whether this novel clinic-based intervention has any initial impact on adherence. This power calculation is based on the study by Okeke et al. in which patients < 75% adherent (measured with electronic monitors) were randomized to a standard counseling intervention vs. regular care [88]. This study demonstrated a 19% ± 20% improvement in adherence in the intervention group. We will aim to enroll 57 patients to allow for a 20% dropout rate; we anticipate this dropout rate given that we are targeting participants who are non-adherent to their recommended medication treatments. We aim to enroll 15 African-American patients to ensure that 25% of our patient population is African-American.

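### The primary outcome is tested by all pairwise paired t tests with no lead contrast, although the study is sized on one pre-post comparison at 5%

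*Protocol article*

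**What the plan says.** The Primary outcome section takes the percentage of doses taken on time, "measured by electronic medication monitors after each intervention". The two components, reminders and then eyeGuide counselling, are given in sequence after a 3-month run-in, so there are at least two post-baseline assessments.

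The Data analysis section compares baseline with post-intervention adherence by paired t "tests for all pair-wise comparisons. Adherence 1 year after the end of all interventions will be evaluated for stability". The one-year follow-up data get plots, paired tests and linear mixed models. Elsewhere in that section, mixed models and GEE on all time points serve predictors, moderators and mediators. The first mediation step tests a slope of adherence over time. An unobserved component model that tolerates missing values is used for cycles and trends.

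The Sample size section sizes one contrast: "We estimate that 46 participants will provide 80% power to detect at least a relative improvement of 15% in adherence". It takes means of 0.7 before and 0.8 after, with an SD of 0.20 at both times, and plans the test "with a type-1 error rate of 5% and assuming a mild correlation of 0.3 between pre- and post-intervention adherences". On enrolment it says "We will aim to enroll 57 patients to allow for a 20% dropout rate". It does not say whether the post-intervention value is the one after reminders or the one after eyeGuide.

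**The concern.** The study is powered for one comparison but commits to testing every pair. With no contrast in the lead, success on any of them can be read as success on the primary outcome. That matters because the article intends the result to show whether the programme has an initial effect, ahead of a randomised trial. The chance that at least one contrast is significant when nothing has changed exceeds the 5% that a reader would carry over from the sample size statement. If a correction were added later, the stated 80% power would no longer apply.

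A second, smaller issue concerns the test itself. A paired t test uses only participants with data in both periods. The article expects 20% dropout, and the section names no missing-data method for these before-after tests.

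**Working it through.** **Inputs (Sample size section).** Difference 0.80 − 0.70 = 0.10; SD 0.20 at each time; correlation 0.3; type-1 error 5%; power 80%; 46 analysed; 57 enrolled for 20% dropout. Sidedness is not stated.

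**1. Reproducing the plan's figure.**
- SD of change = 0.20 × √(2 × (1 − 0.3)) = 0.2366; standardised effect = 0.10 / 0.2366 = 0.423.
- Normal approximation: n = ((1.960 + 0.842) × 0.2366 / 0.10)² ≈ 43.95, so 44.
- Exact two-sided paired t test (noncentral t): n = 46, power 80.1%. A one-sided test would need 37.
- Dropout: 46 / 0.80 = 57.5 against the stated 57; 57 × 0.80 = 45.6 pairs. Power is 79.2% at 45 and 80.1% at 46.

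The 46 therefore reproduces for one two-sided test at 5%, and the loss of power from dropout is already covered.

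**2. Counting the contrasts.** Run-in, reminders and eyeGuide give 3 pairs, of which 2 are against run-in. Adding the post-intervention year would give 6 pairs.

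**3. Chance of at least one false positive, each test at 5%.** The independence figure is 1 − 0.95^k. The tests share data, so 40,000 null trials were simulated with n = 46 and equal correlation between periods (0.3 as stated, 0.6 as a sensitivity value).

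| Contrasts counted | If independent | Simulated, 0.3 | Simulated, 0.6 |
|---|---|---|---|
| 2 (each against run-in) | 9.8% | 9.2% | 8.9% |
| 3 (all pairs, three periods) | 14.3% | 12.3% | 12.2% |
| 6 (all pairs, with the post-year) | 26.5% | 20.5% | 20.8% |

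**4. Cost of a Bonferroni correction, same effect and SD.**

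| Contrasts | Level per test | Power at 46 | n for 80% power | Enrolled at 20% dropout |
|---|---|---|---|---|
| 1 | 0.05 | 80.1% | 46 | 57 (stated) |
| 2 | 0.025 | 70.7% | 56 | 70 |
| 3 | 0.0167 | 64.8% | 62 | 78 |
| 6 | 0.0083 | 54.7% | 72 | 90 |

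One named contrast, or the first contrast in a fixed order, stays on the top row.

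**5. Missing periods.** Someone who leaves during the reminder phase may supply no usable eyeGuide value and so drops out of both eyeGuide pairs. Someone who leaves after month 6 still supplies the run-in/reminders pair. The planned mixed models would use such partial data, but the article attaches them to stability, predictors, moderators and mediators. The one mixed-model test of the intervention is a slope over time, which does not estimate reminders versus run-in or eyeGuide versus reminders.

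**The case against.** The strongest reply is that this is a condensed article about an uncontrolled pilot, and multiplicity rules commonly sit in a statistical analysis plan that is not shown. Silence about a correction is indeed no finding. The point here rests on what is stated: all pairs are to be tested for an outcome sized on one. The pilot label explains why strict familywise control may be unnecessary, but not why no contrast leads, since the article itself claims a power and an error rate.

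Four stronger readings are tempting, and the document does not support them.

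- **That the 5% is wrong.** The rate "with a type-1 error rate of 5% and assuming a mild correlation of 0.3" is given for one pre-post comparison and is never claimed as familywise. It holds for each single test.
- **That the error is four times nominal.** The figure of about 20% needs the one-year data counted as primary. The article handles those data separately, as a question of stability.
- **That dropouts are discarded and only completers analysed.** No such restriction appears. Monitoring is continuous, late leavers contribute earlier pairs, and other planned models use incomplete data.
- **That those who stay are a favourable subset, so the effect is overstated.** The sentence "we anticipate this dropout rate given that we are targeting participants who are non-adherent to their recommended medication treatments" explains why the whole cohort may have high dropout. It does not say that leavers do worse than stayers. Any figure for the bias would need assumed changes in leavers for which the article gives no basis.

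**Conclusion.** The concern holds in a limited form. Testing all three pairs with no lead contrast gives about a 12% chance of at least one false positive on the primary outcome, roughly two and a half times 5%. For the two contrasts against run-in alone it is about 9%. These figures assume no true difference between periods, 46 complete sets of data and equal correlation between periods; moving that correlation from 0.3 to 0.6 hardly changes them. Correcting over three tests would lower power at 46 to about 65%.

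On dropout, the supportable statement is only that the paired t test omits anyone lacking one of the two periods, and that this may bias the change if leaving is related to adherence. Direction and size are unknown. The planned mixed models do not clearly address it, because none is assigned to the primary period contrasts.

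**What to change.** Name one primary contrast. The eyeGuide period (months 6 to 12) versus run-in is a natural candidate, because the power statement draws on a counselling study, but the article does not single it out and the choice is the investigators'. Test the remaining contrasts in a fixed order, each at 5% and stopping at the first that fails, or label them descriptive. Keep the one-year data as a stability analysis outside the primary set.

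Estimate the period contrasts from the linear mixed model already planned, with period as a factor and all enrolled participants included, and keep the paired t tests as a check. This uses partial data and is valid if data are missing at random. It does not remove bias that depends on unobserved outcomes.

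The cost is analysis wording only: 46 analysed and 57 enrolled stand, and no visit or procedure changes. The downside of a fixed order is that later contrasts become descriptive once an earlier one fails.
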